### Health economics analysis

A ‘within-trial’ and model-based economic evaluation will be conducted. These analyses will take the form of a cost-utility analysis. The within-trial analysis will take the perspective of the NHS and personal and social services, but will also take a wider perspective by including costs by the participants and their families. The model-based analysis will take the perspective of the NHS and personal and social services.

### Within-trial analysis

For each trial participant the use of health and social care services will be recorded. The use of services for the initial treatments (medications), including time in hospital, will be collected on the CRF. Also collected on the CRF will be the use of secondary care services such as duration of any hospital stay, number of outpatient visits, use of tests, and any change in medications. Use of primary care services, such as GP visits, will be collected via questionnaire at baseline, 3, 6, 9, 12 and 18 months. Information of further patient costs will be sourced from other relevant RCTs that collected patient costs due to the burden on respondents from collecting this type of data.

Costs for healthcare services will be obtained from standard sources such as NHS reference Healthcare Resource Group (HRG) tariffs, the *British National Formulary*25 (*BNF*) for medications, and Unit Costs of Health and Social Care [20] for primary care usage. Further data will come from the study centres themselves such as the cost of consumables and other equipment used for treatment. The price-year adopted for the base-case analysis will be the year when the final analysis is conducted. For each participant measures of use of resources will be combined with unit costs to provide a cost for that participant.

The relative changes in health-related QoL resultin from reductions in recurrent UTIs, together with any harms associated with each of the treatment strategies and with subsequent treatments for UTIs, will be captured by the EQ5D-5 L. Tariffs will be used to provide values so that the EQ5D-5 L data can be used for decision-making [25]. Health State Utilities from the EQ5D-5 L will be used to estimate QALYs for each participant using the area-under-the-curve approach.

Data on costs and QALYs will be used to estimate the mean cost and QALYs for each intervention group. The cost and QALY data will then be used to estimate incremental costs and QALYs and incremental costs per QALY. These data will be presented as point estimates and bootstrapping techniques will be used to estimate the statistical imprecision surrounding them. The results of this stochastic analysis will be presented as cost and QALY plots and as cost-effectiveness acceptability curves [21].

### Model-based analysis

Drawing upon existing modelling expertise in the Health Economics Group at Newcastle University, an economic model describing recurrent UTIs will be developed. The model will be constructed following guidelines for best practice in economic modelling [22].

The use of services both for the treatment and management for recurrent UTIs will be modelled and the costs of these events will be based upon the estimates for these events derived from within the trial. The trial-based data will be the main source of data for the economic model but it will be supplemented by focussed searches of the literature and health economic databases (e.g. the Centre for the Evaluation of Value and Risk in Health (CEVR) Cost Effectiveness Analysis (CEA) Registry; NHS Economic Evaluation Database).

Discounting will be applied to costs and outcomes at the UK-recommended rate of 3.5% [23]. Further data required for the model relate to the transition and other probabilities of events occurring over the lifetime of patients. These probabilities include the risk of recurrence as well as probabilities of receiving different types of intervention should recurrence occur.

The model will be used to produce estimates of costs and QALYs (from the EQ5D-5 L). Cost-effectiveness will be reported as incremental cost per QALY gained (at both 12 months and over the patient’s lifetime). The model will be probabilistic and distributions will be attached to all parameters, the shape and type of distribution will depend upon the data available and recommendations for good practice in modelling [24]. The results will also be presented as point estimates of costs, effects, incremental costs, QALYS and measures cost-utility. They will also be presented as plots of costs and QALYs derived from the probabilistic analysis and cost-effectiveness acceptability curves. Deterministic sensitivity analyses will be combined with the probabilistic analysis to explore other forms of uncertainty.

### Trial monitoring

Monitoring of study conduct and data collected will be performed by a combination of central review and site monitoring visits to ensure that the study is conducted in accordance with GCP. Study site monitoring will be undertaken by members of the Trial Management Group (TMG). The main areas of focus will include consent, serious adverse events (SAEs) and essential documents in study. Site monitoring will include:All original consent forms will be reviewed as part of the study file; confirmation of the presence of a copy in the patient hospital notes may be requested for 10% participantsAll original consent forms will be compared against the study participant identification listAll reported SAEs will be verified against clinical records (Source Data

Verification (SDV))The presence of essential documents in the ISF and study files will be checkedVerification of primary endpoint data and eligibility data for 10% of participants entered in the study may be requested

Central monitoring will include:All applications for study authorisations and submissions of progress/safety reports will be reviewed for accuracy and completeness, prior to submissionAll documentation essential for study initiation will be reviewed prior to site authorisationStatistical monitoring for outlier sites and unusual data patterns

All monitoring findings will be reported and followed up with the appropriate personnel in a timely manner.

Adverse events (AEs) occurring during trial participation will be recorded and reported in line with GCP guidelines. The expected rate of AEs is low for both treatment arms. All non-serious adverse reactions (ARs) will be recorded in the study database for the duration of the trial. Any SAEs or serious adverse reactions (SARs) will be recorded throughout the duration of the trial in the study database and on the specific trial SAE form.

The trial may be subject to audit by representatives of the sponsor (Newcastle upon Tyne Hospitals NHS Foundation Trust) or inspection by the MHRA or HTA. Each investigator site will permit trial-related monitoring, audits and regulatory inspection including access to all essential and source data relating to the trial.

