**Fig. 1 Fig1:**
[figure not shown]
Trial flow chart

**Table 1 Tab1:** Schedule of procedures

Procedures	Screening	Baseline	Treatment phase						Follow up	
			3 months	6 months	9 months	12 months	At time of UTI	Monthly checks	15 months	18 months
Informed consent		X								
Demographics	X	X^a^								
Medical history		X								
Physical examination		X								
eGFR and LFTs (a sample for DNA will be taken at one of these time points)	X	X^a^	X	X	X	X			X	X
MSU (local laboratory)		X	X	X	X	X	X		X	X
MSU (central laboratory)		X	X	X	X	X	X		X	X
Perineal swab		X		X		X				X
Concomitant medications	X	X^a^								
Eligibility assessment	X									
Randomisation		X								
Dispensing of trial drugs		X	X	X	X					
Compliance			X	X	X	X	X	X	X	X
UTI record							X			
UTI questionnaire			X	X	X	X			X	X
EQ5D-5 L		X	X	X	X	X	X		X	X
Health Resource Use Questionnaire		X	X	X	X	X				X
TQSM						X				X
Adverse event assessments			X	X	X	X	X		X	X
CRF completion	X	X	X	X	X	X	X	X	X	X
Qualitative interviews	X^b^					X^c^				

*CRF* Case Report Form, *DNA* deoxyribonucleic acid, *eGFR* estimated glomerular filtration rate, *EQ5D L* EuroQoL 5 Dimension Questionnaire, *LFT* liver function tests, *MSU* mid-stream urine, *TQSM* Treatment Questionnaire on Satisfaction with Medication, *UTI* urinary tract infection

^a^Screening data values may be used for baseline if taken within 14 days from date of randomisation. ^b^15 patients who declined to participate in main study but consented to interview study. ^c^15 patients who do not complete the treatment and 15 patients who stay in the study up to 6 months post randomisation will be interviewed. Time points will vary

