### Blinding

There is no participant blinding in this study. The members of the local research team that will carry out the follow-up process will not be blinded to the allocated treatment for each participant. We will, however, try to ensure that central trial staff will be unaware of allocated group in data reported during the trial where possible.

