### Sample size calculation

The clinical trial has a planned recruitment target of 240 patients, 120 in each of the treatment arms. If there is an actual difference of 0.6 episodes (in favour of treatment with antibiotics), then two groups of 87 patients are required to be 90% sure that the lower limit of a one-sided 95% confidence interval (or equivalently a 90% two-sided confidence interval) will be above the non-inferiority limit of one UTI episode assuming a standard deviation of 0.9 episodes per year. Total sample size assuming two groups and an attrition rate of 25% = 232, rounded up to 240.

We have discussed extensively the relative merits of non-inferiority against superiority comparison and believe the key issue is that an orally administered urinary antiseptic would be acceptable to the patient group provided that their effectiveness for UTI prevention is no worse than antibiotic prophylaxis and that the burden of adverse effects is similar or better. There is also the key added potential benefit of reduced rates of resistant organisms and subsequent collateral harm to the individual and the community. The sample size calculation is based on the following assumptions:Semi-structured interviews with a patient panel of 12 women identified that any reduction in UTI episodes even by one per year would be deemed worthwhile. Therefore, we have set the minimum clinically important difference between the treatment arms of one UTI per 12 months as our non-inferiority marginThe two existing meta-analyses of studies examining prophylactic antibiotics [6] and methenamine hippurate [7] have quoted mean relative risk of UTI vs placebo of 0.15 and 0.24, respectively. Using these values and data from a local audit (unpublished, *n* = 200) suggesting that the average number of UTI episodes per year in this patient group is 6.5, we have estimated that the difference in number of episodes per year between prophylactic antibiotics and methenamine hippurate to be 0.6 episodes (in favour of antibiotics)The standard deviation of episodes of UTI per year is taken from the placebo groups in the studies included in the Cochrane meta-analyses [4, 10] and has been conservatively estimated at 0.9 episodes per yearThe type-1 error rate for a two group comparison is set at 5%, thus the calculation of a one-sided 95% confidence interval (or a two-sided 90% confidence interval)The attrition rate of participants in this study has been conservatively estimated at 25%

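### The protocol does not settle whether all non-serious adverse events or only drug-attributed reactions are entered in the database, and this open-label trial lists no adverse-effect outcome

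*Protocol article*

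**What the plan says.** The Trial monitoring section of the protocol article makes three statements about recording harms:

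- In general: "Adverse events (AEs) occurring during trial participation will be recorded and reported in line with GCP guidelines".
- For non-serious events: "All non-serious adverse reactions (ARs) will be recorded in the study database for the duration of the trial".
- For serious events: "Any SAEs or serious adverse reactions (SARs) will be recorded throughout the duration of the trial in the study database".

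Table 1 (Schedule of procedures) has a row for "Adverse event assessments", marked at 3, 6, 9, 12, 15 and 18 months and at the time of a UTI.

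On blinding, the article states "There is no participant blinding in this study", and that the local team doing follow-up "will not be blinded to the allocated treatment for each participant".

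The Sample size calculation section explains why non-inferiority was chosen. A urinary antiseptic would be acceptable to patients "provided that their effectiveness for UTI prevention is no worse than antibiotic prophylaxis and that the burden of adverse effects is similar or better". The first half of that condition has a margin, a sample size and an analysis. The second half has no counterpart in Secondary objectives, Primary outcome measures, Secondary outcome measures or Statistical analysis.

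**The concern.** An adverse event is anything untoward that happens; an adverse reaction is an event that someone has attributed to a drug. A database that holds non-serious events only when they have been so attributed measures frequency multiplied by attribution. In an open-label comparison of two drugs with different reputations, attribution can differ between arms even when frequency does not.

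A second problem follows from the design. Women in both arms receive treatment courses of antibiotics for breakthrough UTI, and the trial assumes more such episodes on methenamine. Side effects of those courses belong to the burden of the strategy a woman was allocated to. If reaction means reaction to the trial drug, which the article does not define, they could go unentered.

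At stake is the tolerability half of the article's own acceptability argument. The Statistical Analysis Plan can add tabulations, but it cannot recover events that were never entered.

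**Working it through.** **1. The recording sentences side by side.** For serious events the database rule names events as well as reactions, so causality does not matter. For non-serious events it names reactions alone. If every non-serious event were entered, that sentence would be redundant. Yet the general sentence and Table 1 both speak of adverse events without restriction. The two readings (all events, or reactions) are both open, and they lead to different datasets.

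**2. Who would apply a causality filter.** No section names the assessor. Local staff complete the CRF at visits (Face-to-face appointments) and enter the data (Data handling and record keeping), and they know the allocation (Blinding). No blinded assessor of adverse events is described.

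**3. Which effects are expected in which arm.** The Methenamine hippurate section names nausea, gastrointestinal disturbance, itching and skin rashes. The Antibiotic prophylaxis section names nausea with nitrofurantoin and candidiasis with cefalexin. The section on the current body of evidence reports candidiasis and gastrointestinal symptoms for antibiotics. Gastrointestinal effects are therefore expected in both arms, so attribution could lean either way.

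**4. What the trial is sized on.** The inputs in the Sample size calculation section are margin 1, assumed difference 0.6, SD 0.9, one-sided 5% and 90% power:

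n per group = 2 × (1.645 + 1.282)² × 0.9² / (1 − 0.6)² ≈ 86.7, so 87.

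Then 174 / (1 − 0.25) = 232, rounded up to 240. The plan's figures reproduce. They rest on the UTI outcome alone.

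**5. Size of an attribution effect (assumed inputs).** The article gives no event rate; it says only that the expected rate is low in both arms. Let the true proportion p be the same in both arms and let attribution be a₁ and a₂. The false difference in recorded reactions is p × (a₁ − a₂).

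| True p, both arms | Attribution 50% v 50% | 70% v 50% | 80% v 40% |
|---|---|---|---|
| 10% | 0 | 2 points | 4 points |
| 20% | 0 | 4 points | 8 points |
| 30% | 0 | 6 points | 12 points |
| 50% | 0 | 10 points | 20 points |

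A more extreme contrast, p = 20% with 90% v 30%, gives 18% v 6%.

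For scale, the 95% CI half-width for a difference in the unfiltered proportions is 1.96 × √(2p(1 − p)/m). With m between 87 and 120 per arm it runs from 7.6 points (p = 10%, m = 120) to 14.9 points (p = 50%, m = 87). At low event rates the false difference is smaller than sampling error; at higher rates with strong differential attribution it can exceed it.

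**6. Breakthrough treatment courses.** The plan's assumed difference is 6.5 × (0.24 − 0.15) = 0.585, rounded to 0.6 episodes per year. The primary outcome counts antibiotic-treated UTIs, so each episode implies a treatment course. With 120 women that is 0.6 × 120 = 72 more episodes on methenamine over 12 months (0.6 × 87 ≈ 52 if only 87 are evaluable). At the non-inferiority limit it is 1 × 120 = 120. These are the courses whose side effects a trial-drug definition of reaction could leave out.

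**The case against.** The strongest reply is that the article condenses a longer protocol. Safety recording takes a few sentences here; definitions, causality procedures and the assessor's role would normally be set out in full elsewhere, and safety tables in the analysis plan. The word only does not appear, the general sentence covers all adverse events, and Table 1 schedules event assessments. All of this stands. A reader might infer that non-serious events are entered only when unblinded staff judge them drug-related; the article states neither the restriction nor who judges.

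Harms are also not wholly unmeasured. The within-trial economic analysis says the EQ5D-5L captures them, treatment satisfaction (TQSM) is a secondary outcome, the DMC monitors safety endpoints, and stopping or switching for intolerance is recorded in both arms. This too stands, but none of these is listed as an adverse-event rate compared by arm, and no safety endpoint is named.

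Two further inferences go beyond the text. One is that the bias would favour methenamine; because gastrointestinal effects are named for both treatments, no overall direction follows. The other is that tolerability is what justifies allowing up to one extra UTI per year. The margin is derived from a patient panel, reduced resistance is named as the key added benefit, and the decision rule in Statistical analysis uses the UTI limit alone. The adverse-effect clause is rationale and not a decision rule.

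Condensation does not remove the core. The outcome lists are long and detailed, and choosing outcomes is a matter for the protocol. The unclear recording rule is in the published text.

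**Conclusion.** The point holds as an unclear recording rule combined with a missing outcome; a demonstrated bias is not shown. The Trial monitoring section can be read as entering all non-serious events or only those attributed to a drug. On the second reading, the comparison of non-serious harms between unblinded arms is at risk of attribution bias, and harms from breakthrough courses could drop out. The size depends on event rates and attribution that the article does not give: 2 to 20 points over the assumed range tabulated, and zero if attribution is equal.

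Separately from how the sentences are read, the adverse-effect part of the acceptability rationale has no listed outcome. The UTI non-inferiority analysis is unaffected. The change is worth making because it is cheap and because omitted events cannot be restored at the analysis stage.

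**What to change.** Reconcile the two sentences in Trial monitoring into one rule: every non-serious adverse event found at the assessments in Table 1 is entered in the database whatever its judged causality, with causality held as a separate field. A reaction-only table can still be produced from that field.

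Add two items to Secondary outcome measures, both compared by randomised arm: the proportion of women with any adverse event, and the proportion stopping allocated treatment for intolerance. The second uses information already recorded under Methenamine hippurate, Antibiotic prophylaxis and Assessment of study adherence.

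The cost is modest extra data entry plus protocol wording; no new visit or assessment is needed. Trial status says recruitment has reached its target, so if the reaction-only reading has been in use, events from past visits would have to be retrieved from visit forms or notes where they exist.

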### Trial reporting

Final data cleaning and preparation of tables for analysis, and writing of Background and Methodology sections of the report will commence at month 30 but the results will not be communicated to the PMG and TSC by the trial statistician until after the end of follow-up phase at month 48. These data will be available to the DMC on request or when indicated by the trial statistician.

During this period the health economics team will prepare the structure of the cost-effectiveness analyses using dummy and actual data as it becomes available. Final analysis together with preparation of the introduction and methodology sections of the report and associated peer-reviewed publication will then be performed during months 47–54 with finalisation of the report by end of month 55.

### Dissemination and outputs

The results of the study will be presented at topic-specific national/international conferences and be published in a general medical, infectious diseases or urology themed peer-reviewed journal. The trial will provide high-level evidence to use in new or updates of existing systematic reviews such as those published by Cochrane.

The most significant anticipated outcome from this study will be demonstration of the efficacy of a non-antibiotic treatment for the prevention of recurrent UTIs, methenamine hippurate. If our hypothesis holds true the study will represent a significant step forward in the treatment of recurrent urinary infection, with high-level evidence for the use of a treatment strategy that avoids prolonged antibiotic use which is directly in line with the UK Government’s strategy to combat antimicrobial resistance. It is likely that national and international media will pick up the story and inform the wider public of the results and their significance. We will also engage with relevant NHS managers and other trust representatives to facilitate prompt changes in local practice and promote this alternative preventative treatment for recurrent UTIs. The results will be publicised on both hospital websites and discussed at departmental meetings. The results will be disseminated to members of professional groups, such as BAUS and EAU, through updates and presentations.

Participants will be provided with a lay summary of results. They will also have access to a copy of journal articles through the trial website. Members of our PPI focus groups will review results and they will be involved in writing lay summaries of results for dissemination to relevant patient groups such as the Cystitis and Overactive Bladder Foundation (COB) and the Bladder and Bowel Foundation. We will utilise the COB expertise on how best to deliver these results to the other participants and patient-specific groups. These will be in accessible formats in keeping with equality legislation.

### SPIRIT

This protocol has been written in accordance with the Standard Protocol Items: Recommendations for Interventional Trials (SPIRIT) guidelines. Please refer to the SPIRIT Checklist and Figure (Fig. 2) submitted alongside this publication for further details (see Additional file 1).

**Fig. 2 Fig2:**
[figure not shown]
Standard Protocol Items: Recommendations for Interventional Trials (SPIRIT) Figure for the ALTAR trial

